### Data collection

Generic variables relating to the patient demographics, antenatal care, prehospital care, clinical condition, surgical intervention and outcomes will be collected for all patients in the study (table 1). Specific variables will be collected for each individual condition (online supplementary file 1).

10.1136/bmjopen-2019-030452.supp1Supplementary data

Outcomes and variables have been chosen using published core outcome sets and commonly collected outcomes in systematic reviews and meta-analyses.^22–37^ Collaborators will enter anonymous, deidentified data via the secure internet-based REDCap system. This will be stored on King’s College London REDCap server.

A short survey will be completed by the local study lead and one other collaborating consultant or registrar on the resources and facilities available for neonatal and paediatric surgical care at their centre (online supplementary file 2).

10.1136/bmjopen-2019-030452.supp2Supplementary data

### Data quality

To ensure high quality of data, a detailed protocol for collaborators has been produced and published on the study website (www.globalpaedsurg.com) in 12 languages: English, French, Spanish, Portuguese, German, Italian, Chinese, Arabic, Korean, Lithuanian, Turkish and Russian. Clear and concise definitions have been provided for all data points on the protocol, on the data collection forms and within REDCap when entering the data. A study launch meeting was undertaken where the principal investigator presented the data collection process in detail, demonstrated use of REDCap and answered questions. This was recorded, circulated to all collaborators via email and placed on the website. A frequently asked questions document has been circulated via email and placed on the website. Two meetings were held by the principal investigator to detail the study, data collection process and answer questions among the country leads so they in turn can provide advice and support to local collaborators within their country. Again this was recorded, circulated and placed on the website.

A pilot study of the patient data collection form and institutional survey was undertaken by lead investigators to optimise the study design and to address any feasibility or other barriers to effective data collection and study completion across participating sites. The pilot study commenced on 1 August 2018 for 30 days in English, Spanish and French by 41 collaborator colleagues. The data collection forms were amended following feedback to clarify terminology, add important missing variables or descriptions and correct any translation errors. All translated data collection forms, REDCap and study documentation have been checked and verified by a native speaker for accuracy.

### Data validation

Ten percent of collaborating centres will be selected at random for data validation by an independent research collaborator. The aim will be to determine the numbers of patients eligible during the data collection period to check if any were missed and collect a selection of data again to cross-check for accuracy. Validating questions have been built into the data collection tool. At least 90% of primary and secondary outcomes must be completed for each patient. All collaborators within validating centres will be asked to complete a brief survey regarding their experience with data collection to identify any potential errors and to aid with data interpretation.

### Sample size calculation

A sample size calculation was undertaken using Stata/IC V.15.0 based on Bonferroni correction for multiple testing, assuming 80% power and an overall type 1 error of 5%. The required sample size for each condition has been calculated for the primary outcome of mortality in LMICs compared with HICs and also low, middle and high income countries separately (table 2). Mortality estimations are based on pooled data from published studies on these conditions in low, middle and high income countries, respectively.

**Table 2 T2:** Estimated mortality and sample sizes for low, middle and high income countries and the mean number of cases per month per institution globally

Condition	Mortality LIC (%, n)	Mortality MIC (%, n)	Mortality LMIC combined (%, n)	Mortality HIC (%, n)	Sample size for LIC	Sample size for MIC	Sample size for HIC	Sample size for LMIC vs HIC (per group)	Mean no. cases/ month/ institution (L, M and HIC combined)
OA ±TOF	79.5% (62/78)	41.8% (623/1488)	43.7% (685/1566)	2.7% (6/221)	34	34	23	21	1.02
CDH	–	47.4% (130/274)	47.4% (130/274)	20.4% (201/982)	–	–	–	63	0.54
IA	42.9% (42/98)	40.0% (97/241)	41.0% (139/339)	2.9% (12/407)	6014	6014	25	24	0.63
Gastroschisis	83.1% (211/254)	42.6% (205/481)	56.6% (416/735)	3.7% (28/748)	29	29	24	15	0.85
Exomphalos	25.5% (41/161)	31.9% (132/414)	30.1% (173/575)	12.7% (40/316)	1040	1040	196	115	0.63
ARM	26.3% (26/99)	17.5% (243/1391)	18.1% (269/1490)	3% (14/462)	460	460	90	85	1.34
Hirschsprung’s disease	19.1% (33/173)	16.8% (55/328)	17.6% (88/501)	2.3% (43/1897)	5802	5802	85	79	2.21

ARM, anorectal malformation; CDH, congenital diaphragmatic hernia; HIC, high income countries; IA, intestinal atresia; LIC, low income countries; LMIC, low and middle income countries; MIC, middle income countries; OA, oesophageal atresia; TOF, tracheo-oesophageal fistula.

Based on the patient numbers included in the previously undertaken PaedSurg Africa study, which used a similar study design, the estimated sample sizes to detect a significant difference between LMICs and HICs in this study are achievable.^11^

### Estimated study population

The mean number of cases presenting to an institution per month for each study condition was estimated from published studies across all income settings (table 2). On average, most institutions caring for patients with these conditions receive 1–2 new cases per month; each participating institution would expect approximately 7–14 new cases in the study per month although this can vary. The aim is to include a minimum of 365 months of data; 183 months from LMICs and 183 months from HICs. This should ensure enough cases of exomphalos to determine a significant difference between LMICs and HICs; fewer months of data are required to determine significant differences between other study conditions. An up-to-date total of patient numbers within the study will be maintained on the study website.

### Data analysis

#### Patient and institutional data

Data will be analysed using Stata and SAS V.9.4 (Cary, North Carolina, USA). Missing data for the covariates will be analysed to determine whether it is related to the outcome and either complete-case analyses or multiple imputation techniques will be used for analyses accordingly.

Significant differences in mortality between LMICs and HICs will be determined for each of the study conditions using Χ^2^ analysis, or Fischer’s exact test if either group contains <10 patients. World Bank classification of low, middle and high income countries during the fiscal year 2018 will be used.^38^

Univariate logistic regression analyses will be conducted between covariates and the primary outcome of mortality. Based on the results, covariates with a p value <0.10 will be included in the multivariate model. The final multi-level multivariate logistic model will be determined using stepwise backward elimination to interventions and peri-operative factors affecting outcomes. Data will be adjusted for confounding factors and effect modifiers. Potential confounders include gestation age at birth, weight, time from birth to presentation and American Society of Anesthesiologists score at the time of primary intervention. Potential effect modifiers include administration of peri-operative antibiotics, fluid resuscitation, thermal control and provision of other condition-specific neonatal care such as parenteral nutrition in neonates with gastroschisis.

Multi-level multivariate logistic regression analysis will also be undertaken to identify institutional factors affecting mortality with adjustment for confounders. P<0.05 will be deemed significant.

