## Objectives

To compare the mortality and post-intervention complications of a selection of common congenital anomalies involving the gastrointestinal tract in LMICs and HICs globally.To identify patient-level and hospital-level factors affecting outcomes that be modified to improve care.To establish a research collaboration consisting of children’s surgical care providers across the world to help enhance research capacity and to create a platform for ongoing collaborative research and intervention studies aimed at improving outcomes.To raise awareness and provide advocacy for neonatal and paediatric surgical care within global health prioritisation, planning, policy and funding.

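### As written, adjustment for the named confounders depends on P values, and many factors are judged at P<0.05 with no multiplicity control

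*Protocol article*

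**What the plan says.** All of this is in the protocol article, Data analysis, under Patient and institutional data, unless another section is named.

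- Screen: "Univariate logistic regression analyses will be conducted between covariates and the primary outcome of mortality", and on that basis "covariates with a p value <0.10 will be included in the multivariate model".
- Reduction: "The final multi-level multivariate logistic model will be determined using stepwise backward elimination". The sentence goes on to interventions and peri-operative factors, but a verb seems to be missing. No removal threshold is given.
- Adjustment: "Data will be adjusted for confounding factors and effect modifiers". The list of confounders is introduced thus: "Potential confounders include gestation age at birth, weight, time from birth to presentation and American Society of Anesthesiologists score".
- A further multilevel model looks for institutional factors, again with adjustment for confounders.
- Inference: "P<0.05 will be deemed significant".

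These models serve the second objective: "To identify patient-level and hospital-level factors affecting outcomes that be modified to improve care". Bonferroni correction appears only under Sample size calculation. The article does not say whether the models are fitted per condition or on the pooled cohort.

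**The concern.** Whether a variable confounds an exposure depends on its relation to both exposure and outcome. Its own crude P value does not settle that. In a small group a real confounder can miss P<0.10 by chance, and in a group of any size it can be masked by correlation with another risk factor. Once it is gone, factors correlated with it take over part of its effect and can look like targets for improvement. The rule as written allows this for the very four variables the plan says it will adjust for.

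The second issue is separate. Table 1 and the institutional survey supply many candidate factors, and each is judged at the same 0.05 level with no stated control over the list. The findings are meant to guide changes in care and later interventional studies, so false or exaggerated factors would carry forward.

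**Working it through.** **1. The plan's own figures.** The article gives no sample size for the regression models. The only design figures are the per-group sizes for LMIC versus HIC in Table 2. With the usual two-proportion formula (pooled variance under the null, 80% power, two-sided alpha 0.05/3, no continuity correction) they come out as 21, 63, 24, 15, 115, 86 and 79. The printed values are 21, 63, 24, 15, 115, 85 and 79. The divisor of 3 is inferred from the fit. These sizes were set for the crude comparison.

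**2. Sizes the models would have.** Inputs are cases per month per institution and mortality from Table 2, and 183 months in each income group from Estimated study population.
- Exomphalos: 0.63 × 366 ≈ 231 patients; deaths 0.63 × 183 × (0.301 + 0.127) ≈ 49, or 21.4%.
- Anorectal malformation: 1.34 × 366 ≈ 490 patients; deaths 1.34 × 183 × (0.181 + 0.030) ≈ 52, or 10.5%.
- All conditions: (1.02 + 0.54 + 0.63 + 0.85 + 0.63 + 1.34 + 2.21) × 365 = 7.22 × 365 ≈ 2,635.

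**3. Loss of true confounders.** The stated procedure was simulated with 400 runs per scenario. Assumptions: a single-level logistic model, removal at P≥0.05, four true confounders (two with OR 1.5 per SD, two with OR 1.3 per SD) and 20 null factors. Correlation among the confounders was 0, 0.2 or 0.3. In the last case one confounder has the opposite sign and is therefore masked.

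| Size | OR 1.5 lost | OR 1.3 lost (unmasked) | Masked confounder lost |
|---|---|---|---|
| 230 | 32–53% | 63–78% | 98% |
| 490 | 26–43% | 61–69% | 98% |
| 2,600 | 0% | 0–2% | 72% (71% already at the screen) |

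A separate simulation at 231 and 490 lost the OR 1.5 confounder in 18–45% of runs, so the overall range is 18–53%. Selected true effects were exaggerated by a factor of 1.3 to 1.6 on the log-OR scale at 230 to 490 patients.

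**4. Null factors standing in for a dropped confounder.** Here there are 16 null factors, four of them each correlated with one confounder. Chance that such a proxy is kept:

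| Size | Correlation | Stated rule | Four confounders forced in |
|---|---|---|---|
| 231 | 0.7 | 10.2% | 3.1% |
| 490 | 0.7 | 9.9% | 2.6% |
| 231 | 0.5 | 5.6% | 2.3% |
| 490 | 0.5 | 6.4% | 3.2% |
| 2,635 | 0.7 | 5.1% | 4.7% |

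The separate simulation gave about 11% against 1–3%. In the forced-in column the factors themselves still pass the P<0.10 screen, which helps keep those values below 5%. A full model with no selection at all kept the proxy in 6.9% (n=231) and 5.1% (n=490) at correlation 0.7. Without screening, then, the rate to expect is about the nominal 5% per factor before multiplicity control.

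**5. Multiplicity.** For k independent null factors in a fixed model, P(at least one at P<0.05) = 1 − 0.95^k, which is 40% for k = 10, 64% for k = 20 and 79% for k = 30. The stated procedure with 20 null factors, and either no true effects or uncorrelated confounders, gave 61–69%. In the setting of step 4 at correlation 0.7, forcing the confounders in lowered the chance of any false factor only from 64% to 49% (n=231) and from 66% to 49% (n=490).

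**The case against.** The strongest reply is that adjustment for confounders is promised without condition directly after the selection rule, and that elimination is aimed at "will be determined using stepwise backward elimination to interventions and peri-operative factors affecting outcomes". On that reading factors are selected while confounders are simply adjusted for, and forced-in terms are a detail for a statistical analysis plan that is not shown. The authors may well intend this. But the screen is stated for covariates generally, the elimination determines the final model, and no sentence exempts the named variables. The article fixes a rule that conflicts with its own promise, so this is more than an omitted detail.

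Several stronger readings are tempting, and the documents do not support them.
- A reader might blame the roughly 64% false-factor rate on screening and elimination. A fixed model with 20 null factors gives the same figure. It is plain multiplicity.
- A reader might take the 34 rows of Table 1 other than survival as null candidates and arrive at 1 − 0.95^34 = 83%. Seven of those rows are administrative items or secondary outcomes, four are the named confounders and one is study condition. That leaves 22, and 1 − 0.95^22 = 68% only if all were null and independent, which is unrealistic for items such as sepsis on arrival. The article does not say that every item is a candidate.
- A reader might use n=115 for exomphalos. That is a per-group figure; the condition would supply about 230 patients.
- A reader might say the confidence intervals will be too narrow. The article does not mention intervals for these models.
- A reader might say that study condition has been left out. The list of confounders is not exhaustive. With HIC mortality from 2.3% to 20.4% in Table 2, condition would probably pass the screen in pooled data, and it cannot confound a per-condition model. It is unprotected by rule, but not excluded.

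**Conclusion.** The concern holds in a limited form. As written, adjustment for four named confounders depends on P values, which conflicts with the plan's statement that it will adjust for them. The practical effect depends on a choice the article leaves open. If models are per condition, moderate confounders would often be lost and their proxies sometimes reported as factors. If the cohort is pooled, the loss is near zero except for a masked confounder. The lack of multiplicity control is a distinct weakness that applies either way.

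The percentages are illustrative. They rest on assumed effect sizes, correlations, number of null factors, a 0.05 removal threshold and a single-level model. The excess of retained proxies is clear at correlation 0.7 and modest at 0.5. The chi-squared or Fisher comparison of LMIC with HIC mortality is not touched, so the point should be corrected but does not undermine the primary comparison.

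**What to change.** 1. State that gestational age, weight, delay from birth to presentation, ASA score and income group, plus study condition in any pooled model, are exempt from both the screen and the elimination and are always in the model. Say whether models are pooled or per condition.
2. List the modifiable patient-level and institutional factors in advance. Estimate each against that fixed set instead of selecting by P value.
3. Apply Holm or false-discovery control across the list, or label the results exploratory. Step 1 alone is not enough, since it still leaves about a 49% chance of at least one false factor in the simulated settings.

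The change is to wording only and needs no new data. The price is slightly wider intervals and fewer nominally significant factors. Two practical points need a sentence each. Table 1 codes ASA as not applicable when there was no intervention, so the plan must say how those patients enter the model. With about 49 deaths expected in exomphalos, the fixed set should use few parameters there.

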## Introduction

In 2015, the Global Burden of Disease study concluded congenital anomalies (also known as congenital malformations, congenital abnormalities or birth defects) to be the fifth leading cause of death in children <5 years of age globally.^1^ This equates to approximately half a million deaths from congenital anomalies each year, 97% of which occur in low and middle income countries (LMICs). Indeed, this is likely to be an underestimation of the actual number of deaths due to underdiagnosis of neonates with congenital anomalies who die in the community and a lack of death certification in many LMICs.^2^ Not only is the mortality rate higher in LMICs, but the prevalence is also higher due to micronutrient deficiencies, infections and teratogens during pregnancy resulting in more cases and a lack of antenatal diagnosis prohibiting terminations.^3 4^ There is limited research and a lack of congenital anomaly registries in LMICs, and hence they have received very little global attention.^5^

The conditions forming the focus of this study (box 1) constitute a selection of the most common life-threatening congenital anomalies during the neonatal period, which involve the gastrointestinal tract. They each have an incidence of 1/2000 to 1/5000, they collectively form up to 40% of emergency neonatal surgery and associated mortality can be in excess of 50% in many LMICs.^6–9^ Disparities in outcomes globally can be stark; for example, the mortality from gastroschisis is 75%–100% in many LMICs compared with 4% or less in high income countries (HICs).^10–12^ Reasons for poor outcomes include a lack of antenatal diagnosis, delayed presentation, limited neonatal transport and in-hospital resources, a dearth of trained support personnel and a lack of intensive care and parenteral nutrition for neonates.^9 13 14^ In Uganda, it was calculated that only 3.5% of the need for neonatal surgery was met by the healthcare system.^8^

Box 1Congenital anomalies in the Global PaedSurg StudyOesophageal atresia ± tracheo-oesophageal fistulaCongenital diaphragmatic herniaIntestinal atresiaGastroschisisExomphalosAnorectal malformationHirschsprung’s disease

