**Antenatal care and delivery**	
Antenatal ultrasound undertaken? If the condition was diagnosed antenatally, at what gestational age?	Yes: study condition diagnosed, Yes: problem identified but study condition not diagnosed, Yes: no problem identified, No. Please round up to the nearest week. If the patient has more than one study condition, please note the gestational age at which one or more of the conditions was first diagnosed.
Mode of transport to hospital? Where did the patient present from? If other, please specify.	Ambulance, Other transport provided by the health service, Patient's own transport, Born within the hospital. Home, Community Clinic, General Practice, District Hospital, Other, Unknown. District hospital includes secondary-level healthcare, provincial hospital, general hospital, general mission hospital or regional hospital. It has general anaesthesia and can provide general surgical care.
Type of delivery:	Vaginal (spontaneous), Vaginal (induced), Caesarean section (elective), Caesarean section (urgent/non-elective), Unknown. Vaginal delivery includes those requiring forceps and ventouse.

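### Time from birth to presentation is a sound confounder for in-hospital care, but as a blanket adjuster it can attenuate the pre-hospital factors whose effects it may carry

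*Protocol article*

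**What the plan says.** The Objectives of the protocol article include "To identify patient-level and hospital-level factors affecting outcomes that be modified to improve care". The Introduction names the likely culprits: "Reasons for poor outcomes include a lack of antenatal diagnosis, delayed presentation, limited neonatal transport and in-hospital resources".

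Table 1 collects the matching variables for every patient. Distance from home and age at presentation are under Demographics. Antenatal ultrasound with its result, transport and referral origin are under Antenatal care and delivery ("Mode of transport to hospital? Where did the patient present from"). Babies born in the study hospital are coded 0 for both age at presentation and distance, and they have their own transport category.

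The section Patient and institutional data sets the modelling rules:

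- Entry: "covariates with a p value <0.10 will be included in the multivariate model".
- Selection: "stepwise backward elimination to interventions and peri-operative factors affecting outcomes".
- Adjustment: "Data will be adjusted for confounding factors and effect modifiers".
- Confounder list: "Potential confounders include gestation age at birth, weight, time from birth to presentation and American Society of Anesthesiologists score".

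A second multilevel model, for institutional factors, is also adjusted for confounders. The article describes no other patient-level model and no separate adjustment set for pre-hospital factors.

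**The concern.** Whether delay is a confounder depends on the exposure. Antibiotics, fluids and warming are given after the child arrives, so delay precedes them, may influence both treatment and death, and should be adjusted for.

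For antenatal diagnosis, referral origin, transport and distance the order is the other way round. These factors help to determine how soon the child arrives. An antenatal diagnosis that leads to delivery at the surgical centre is recorded as zero delay, and the model then conditions on that zero. Part of the benefit is adjusted away.

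Nothing in the entry rule keeps these variables out, and the second objective is wide enough to take them in. What is at stake is the advice the study gives on modifiable factors: a pre-hospital measure could appear weaker than it is, or be missing from the final model.

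**Working it through.** The plan states no figure on this point, so there is none to reproduce. The check is a set of logistic simulations. All coefficients are assumptions.

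**A. Protective exposure (antenatal diagnosis, 30% of patients), n = 400,000 per scenario**

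log delay = log(24) + d·A + N(0, SD 1.2)

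logit(death) = −1.9 + b·log delay + u·A

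Here d is the effect of diagnosis on log delay, b the effect of log delay on death, and u the direct effect of diagnosis. The delay-adjusted odds ratio (OR) must be close to exp(u). The total OR must be near exp(d·b + u), pulled slightly towards 1 because odds ratios do not collapse. Where repeat runs differed, both values are shown.

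| d, b, u | exp(d·b+u) | Total OR | Delay-adjusted OR |
|---|---|---|---|
| −2, 0.4, 0 | exp(−0.8) = 0.45 | 0.46 | 1.00 |
| −1.5, 0.3, 0 | exp(−0.45) = 0.64 | 0.65 | 1.00 |
| −1, 0.3, 0 | exp(−0.3) = 0.74 | 0.74–0.76 | 0.99–1.02 |
| −2, 0.4, −0.3 | exp(−1.1) = 0.33 | 0.35 | 0.74 |
| −2, 0.4, +0.3 | exp(−0.5) = 0.61 | 0.61–0.63 | 1.34–1.37 |

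In the first row mortality is 20% with antenatal diagnosis and 36% without. The first three rows give a null only because u was set to 0. The last row reverses only because diagnosed cases were assumed to be more severe.

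**B. Harmful exposure (no diagnosis or poor transport, 50% of patients), n = 400,000**

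D = a·A + g·U + N(0,1)

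logit(death) = −1 + c·A + m·D + h·U

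D is log delay and U is unmeasured severity.

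| Scenario | c, m, a, g, h | Without delay | With delay |
|---|---|---|---|
| Full mediation | 0, 0.5, 1.5, 0, 0 | 2.05 | 1.00 |
| Partial mediation | 0.4, 0.5, 1.0, 0, 0 | 2.33 | 1.48 |
| Mostly direct | 0.7, 0.3, 0.5, 0, 0 | 2.31 | 2.03 |
| Full mediation, sicker children later | 0, 0.5, 1.5, 0.7, 0.7 | 1.82 | 0.63 |
| Full mediation, sicker children earlier | 0, 0.5, 1.5, −0.7, 0.7 | 2.00 | 1.59 |

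**C. In-hospital factor, with delay a true confounder**

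D ~ N(0,1); logit P(H) = 0.8·D; logit(death) = −1 + 0.4·H + 0.5·D. The true conditional OR is exp(0.4) = 1.49. The estimate is 2.06 unadjusted and 1.50 adjusted for delay, so adjustment is needed here.

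**D. Effect of the selection rule**

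Estimated study population gives at least 365 months of data at about 7 cases or more, and 365 × 7 = 2,555. With n = 2,500, one exposure plus delay, and P<0.05 assumed for retention, 300 runs gave:

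- first row of A: the exposure passed the p<0.10 screen in 100% of runs and was then eliminated in 94%;
- fourth row of A (direct benefit added): it was still eliminated in 39%.

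**The case against.** The strongest defence is that the model's declared target is interventions and peri-operative factors, with a second model for institutional factors. For those, listing delay is correct, and part C shows that omitting it would be an error. The analysis section never names antenatal diagnosis, transport, referral origin or distance as exposures of interest, and nothing says that their coefficients would be read as total effects. This stands, and it limits the point to the case where those variables enter the same model. The entry rule allows that case, and the second objective invites it.

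A reader might infer that pre-hospital factors will look harmless or even harmful. The documents do not support that. A null needs complete mediation, and a reversal needs an added severity effect or an unmeasured common cause acting in one direction. Under partial mediation the harm stays visible (1.48 and 2.03 in part B). The Introduction lists its reasons side by side without a causal order, so the pathway itself is an assumption.

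The confounders are called potential, and elimination may remove delay. That is true, but elimination can equally remove a mediated exposure while keeping delay, as part D shows. The planned univariate regressions will give associations not adjusted for delay, and delay itself may emerge as a factor worth acting on. Both help, but neither gives a confounder-adjusted total effect of a pre-hospital factor.

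The separate models proposed here are not free of bias. Late presentation can reflect milder disease: the inclusion criteria allow Hirschsprung's disease first presenting at several months. Late presenters have also survived to present, and the limitations admit that some children never reach care. This stands and must be reported with the estimates.

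Exposure-specific adjustment could be set out in a fuller plan that is not shown. If so, the point is met. What is raised here is the confounder list and entry rule that the article does state.

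**Conclusion.** The point holds in a limited form. Naming delay as a confounder is right for in-hospital and institutional factors. Applied through one list and one unrestricted screen, it is not suited to antenatal diagnosis, referral origin, transport or distance, whose adjusted coefficients would not be total effects.

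The expected consequence is attenuation by the share of the effect that runs through delay, with a real chance of elimination from the final model. In the assumed scenarios without unmeasured severity or an added severity term, this ranges from slight (2.31 to 2.03) to complete (0.46 to 1.00). The direction rests on one causal assumption, that these factors change time to presentation and that delay affects death. The size rests on coefficients that the documents do not give. The comparison of mortality between LMICs and HICs by condition is untouched. This is an inexpensive improvement to the secondary modelling, not a flaw in the study's main comparison.

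**What to change.** Make the adjustment set depend on the exposure.

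1. Keep time from birth to presentation in the models of interventions, peri-operative factors and institutional factors.
2. For antenatal diagnosis, referral origin, transport and distance, report separate multilevel logistic models. Adjust these for characteristics fixed at birth (condition, gestational age, associated anomalies) and leave out time to presentation and clinical status on arrival. Weight in Table 1 is measured on the day of presentation, so it does not belong in this set.
3. State that total effects of pre-hospital factors are not to be read from the in-hospital-care model.
4. State beside the pre-hospital estimates that they remain open to confounding by severity and to selection by survival to presentation.

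The cost is a few sentences in the analysis plan, a few extra models on data already being collected, and one more results table. No new data are needed.
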